## 4 OBJECTIVES AND ENDPOINTS

### 4.1 SCREENING STUDY (CROSS-SECTIONAL SURVEY SOURCE POPULATION) (N~ 4,720)

| Primary objective                                                                                                                                                                          | Primary endpoint                                                                                                                                                                                                                                                      |
|--------------------------------------------------------------------------------------------------------------------------------------------------------------------------------------------|-----------------------------------------------------------------------------------------------------------------------------------------------------------------------------------------------------------------------------------------------------------------------|
| 
 
To determine if malaria infection is predictive of the prevalence of SARS-CoV-2, adjusted for other risk factors of SARS-CoV-2 infection
 
 | 
 
Cross-sectional comparison of the proportion of participants with SARS-CoV-2 in the source population among participants with and without malaria infection expressed as the prevalence ratio for COVID-19 (95% CI)
 
 |
| Secondary objectives                                                                                                                                                                       | Secondary endpoints                                                                                                                                                                                                                                                   |
| 
 
To determine the demographic and clinical risk factor for the prevalence of SARS-CoV-2 infection
 
                                         | 
 
Cross-sectional comparison of demographic and clinical risk factors of SARS-CoV-2 in the source population expressed as a prevalence ratio for COVID-19 (95% CI)
 
                                                    |

### 4.2 COVID-19 COHORT (N~708)

| Primary objective                                                                                                                                                                       | Primary endpoint                                                                                                                                                                                                                                                                                                                                                                                                          |
|-----------------------------------------------------------------------------------------------------------------------------------------------------------------------------------------|---------------------------------------------------------------------------------------------------------------------------------------------------------------------------------------------------------------------------------------------------------------------------------------------------------------------------------------------------------------------------------------------------------------------------|
| 
 
To determine if malaria infection affects COVID-19 severity
 
                                                                           | 
 
Comparison of the severity of COVID-19 by day-28 in cases with and without malaria using the WHO clinical progression scale
 
                                                                                                                                                                                                                                             |
| Secondary objectives                                                                                                                                                                    | Secondary endpoints                                                                                                                                                                                                                                                                                                                                                                                                       |
| 
 
To determine if malaria infection affects COVID-19 disease presentation and duration
 
                                                  | 
 
Symptoms and duration of COVID-19 by day-28 in cases with and without malaria
 
                                                                                                                                                                                                                                                                                           |
| 
 
To determine if malaria infection in COVID-19 patients alters the antibody response to SARS-CoV-2 infection
 
                           | 
 
Cumulative seroconversion rates* (total antibody, IgG, IgM, IgA) by days 7, 14, 21, 28, and total antibody, IgG, IgM, IgA antibody titres against SARS-CoV-2 by day-28 expressed as the geometric mean, maximum, and change from baseline
 
Seroreversion rates for IgG, IgM, IgA and geometric mean antibody titres against SARS-CoV-2 by month 3, 6 and 12
 
     |
| 
 
To determine if malaria infection in COVID-19 alters the inflammatory, genomic, and cellular immune responses to SARS-CoV-2 infection
 
 | 
 
Multiplex serum cytokine markers; Transcriptional profiling (gene expression) of whole blood; Fixed whole blood for T and B cell markers by day-28
 
                                                                                                                                                                                                                      |
| 
 
To determine if malaria infection in COVID-19 alters the viral load or duration of SARS-CoV-2 infection
 
                               | 
 
Median viral load of SARS-CoV-2 detected from mid-nasal swabs by PCR
 
Cumulative incidence of SARS-CoV-2 clearance (defined as the proportion of participants with negative nasal swabs) by days 7, 14, 21 and 28
 
Time to clearance of nasal SARS-CoV-2, defined as negative SARS-CoV-2 RNA PCR tests (swabs collected on days 1, 3, 7, 14, 21 and 28)
 
 |

### 4.3 NESTED MALARIA TREATMENT TRIAL IN THE COVID-19 COHORT STUDY (N~142)

| Primary objective                                                                                                                                                                                                                                                                    | Primary endpoint                                                                                                                                                                                                                                                                                                                                                                                                       |
|--------------------------------------------------------------------------------------------------------------------------------------------------------------------------------------------------------------------------------------------------------------------------------------|------------------------------------------------------------------------------------------------------------------------------------------------------------------------------------------------------------------------------------------------------------------------------------------------------------------------------------------------------------------------------------------------------------------------|
| 
 
To determine if pyronaridine-artesunate compared to artemether-lumefantrine reduces early SARS-CoV-2 viral shedding
 
                                                                                                                | 
 
Incidence of SARS-CoV-2 clearance (defined as the proportion of participants with a negative nasal swab) on Day 7 after the start of treatment
 
                                                                                                                                                                                                                       |
| Secondary objectives                                                                                                                                                                                                                                                                 | Secondary endpoints                                                                                                                                                                                                                                                                                                                                                                                                    |
| 
 
To determine if pyronaridine-artesunate compared to artemether-lumefantrine alters the viral load and/or the duration of SARS-CoV-2 viral shedding
 
                                                                                 | 
 
Median viral load of SARS-CoV-2 detected from mid-nasal swabs by PCR
 
Cumulative incidence of SARS-CoV-2 clearance (defined as the proportion of participants with negative nasal swabs) by days 14, 21 and 28
 
Time to clearance of nasal SARS-CoV-2, defined as negative SARS-CoV-2 RNA PCR tests (swabs collected on days 1, 3, 7, 14, 21 and 28)
 
 |
| 
 
To determine if treatment of malaria infection with pyronaridine-artesunate in COVID-19 patients alters the antibody response to SARS-CoV-2 infection compared to treatment with artemether-lumefantrine
 
                           | 
 
Cumulative seroconversion rates (IgG, IgM, IgA) by days 7, 14, 21 and 28, and IgG, IgM, IgA antibody titres against SARS-CoV-2 by day-28 expressed as the geometric mean, maximum, and change from baseline
 
                                                                                                                                                          |
| 
 
To determine if treatment of malaria infection with pyronaridine-artesunate in COVID-19 alters the inflammatory, genomic, and cellular immune responses to SARS-CoV-2 infection compared to treatment with artemether-lumefantrine
 
 | 
 
Multiplex serum cytokine markers; Transcriptional profiling (gene expression) of whole blood; Fixed whole blood for T and B cell markers by day-28
 
                                                                                                                                                                                                                   |
| 
 
To compare the clinical and parasitological efficacy of pyronaridine-artesunate versus AL in COVID-19 patient coinfecting with malaria parasites.
 
                                                                                  | 
 
The proportion with early treatment failure, late clinical failure, late parasitological failure or an adequate clinical and parasitological response. Recrudescence will be differentiated from new infection by genotyping of malaria parasites by day 42
 
                                                                                                          |
| 
 
To determine if pyronaridine-artesunate compared to artemether-lumefantrine alters COVID-19 disease progression and severity
 
                                                                                                       | 
 
COVID-19 symptoms, duration and severity as defined by a severity index score by day 28
 
The proportion of days with a fever after randomization
 
The proportion of days with respiratory symptoms after randomization
 
                                                                                                                               |
| 
 
To test the safety of pyronaridine-artesunate compared to artemether-lumefantrine in COVID-19 patient coinfecting with malaria parasites
 
                                                                                           | 
 
The cumulative proportion of treatment-related adverse events and serious adverse events and adverse events resulting in treatment discontinuation by day 7
 
                                                                                                                                                                                                          |
| 
* The cumulative seroconversion rate is defined as the proportion of participants with a positive antibody test per period among those with a negative antibody test on enrolment.
                                                                                            |                                                                                                                                                                                                                                                                                                                                                                                                                        |

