| Study type             | 
Interventional and observational
 
Observational: screening study (cross-sectional survey, source population) Screening study (cross-sectional survey source population) Cross-sectional assessment of a source population consisting of suspected COVID-19 cases and their contacts and high-risk populations. Observational cohort: Participants with COVID-19 with and without malaria will be followed for 28 days, and then at 3, 6, and 12 months.
 
Interventional: Covid-19 cases co-infected with malaria will be enrolled in a nested malaria treatment trial. Allocation: randomised; intervention model: parallel assignment; arms: 2; allocation ratio: 1:1; stratified by site (i.e. hospital or clinic) and by the presence of symptoms at enrolment consistent with COVID-19 (asymptomatic vs symptomatic). Masking: blinding of primary outcome assessor (off-site laboratory-based staff)
 
Primary purpose: Treatment and prevention
 
Phase-III
 |
| Date first enrolment   | [dd mmm yyyy]                                                                                                                                                                                                                                                                                                                                                                                                                                                                                                                                                                                                                                                                                                                                                                                                                                                                                                                                                                                  |

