### 9.1.1 Pre-screening with point of contact (POC) SARS-CoV-2 antigen tests

The screening study (cross-sectional survey, source population) includes pre-screening with an experimental POC SARS-CoV-2 antigen tests and Government approved antigen tests. At the time of writing (September 2020), there are no approved SARS-CoV-2 antigen tests yet in Kenya or Burkina, but this may change during the course of the study. We will follow the national guidelines in each country. In Kenya GeneXpert, antigen-RDT and PCR results are considered for definitive diagnosis of COVID-19. If a participant tests COVID positive for any rapid antigen tests, GeneXpert, or PCR, the participant shall be enrolled.

Eligible patients with both a positive SARS-CoV-2 test and a positive malaria test on Day-0 require malaria treatment that same day and will be invited to enrol in the COVID-19 cohort study and the nested malaria treatment trial on Day-0; i.e. prior to knowing the SARS-CoV-2 PCR results (see 9.2.1.3, Nested malaria treatment trial, page 43). Patients with a positive antigen test but negative for malaria will be invited to participate in the COVID-19 cohort study and can choose whether to enrol that same day (Day-0) or wait until the confirmatory PCR results become available (typically on Day-1).

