### 10.2 BIOLOGICAL SAMPLES

#### 10.2.1 Mid-nasal swab

We will take two mid-nasal swab sample for research specific molecular detection of SARS-CoV-2 (for later batch analysis, not for patient care). Mid-nasal cavity are less intrusive than nasopharyngeal swabs with less potential for the patient to sneeze, cough, or gag and provide a more comfortable patient experience. Mid-nasal swabs were shown to have a sensitivity of 94% compared to nasopharyngeal swabs.

The nasal swabs will be placed in the plastic tube with transport media, which will be placed into a labelled specimen bag, pre-packaged with an absorbent sheet. One swab will be placed in viral transport media (e.g. DNA/RNA Shield), the other in 0.9% saline, or phosphate-buffered saline, which have been shown to be equivalent for storage of SARS-CoV-2 samples based on validated assays. Previous testing has demonstrated that respiratory viral ribonucleic acid (RNA) is stable in room temperature for up to 1 week. Samples will be stored at -80°C prior to use.

Samples eluted from swabs will be subjected to RNA amplification and tested for SARS-CoV-2 and used for viral invasion assays.

Viral RNA loads will be estimated using quantitative real-time reverse-transcriptase polymerase chain reaction (qRT-PCR) assays which target multiple sites in the SARS-CoV-2 genome, including at least one position each in the Orf1ab and N regions. Validated and standardised quantified plasmid and in vitro transcript RNA controls will be made available to all partner laboratories for use in viral RNA load estimation.

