### 11.1.3 Nested malaria treatment trial

Approximately 54 participants in Kenya are expected to have malaria (15% of 354) and will be enrolled in the nested treatment study comparing AL vs pyronaridine-artesunate (1:1). The corresponding number in Burkina Faso is 88 (25% of 354). Thus 142 pooled across the two countries. A study of 142 participants has 80% power to detect a 22.2% absolute increase in viral clearance by day-7 from 20% in the artemether-lumefantrine arm to 42.2% in the pyronaridine-artesunate arm ( $RR=2.11$ ), assuming a 5% loss to follow-up by day 7 (134 completers) (two-sided  $\alpha=0.05$ ). The 20% viral clearance rate by day=7 in the control arm (artemether-lumefantrine) is based on a previous trial.

Similarly, a sample of 142 participants has 80% power to detect a 50% relative decrease ( $RR=0.50$ ) or increase ( $RR=1.50$ ) in the cumulative seroconversion rate by day 14 from 50% in the artemether-lumefantrine arm (control arm) to either 25% or 75% in the pyronaridine-artesunate arm, assuming a 10% loss to follow-up (128 completers). The seroconversion rate of 50% by day 14 is based on previous observational COVID-19 studies in China.

Although the nested malaria treatment trial will be exploratory in nature, the study design includes the option to conduct interim analyses as part of the emergency response to the pandemic to ensure that promising findings can be shared early (see 11.2.5.3, Interim analysis and early stopping rule for efficacy, page 59).

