#### **11.2.5.2 Assessment of efficacy**

Similar approaches as for the COVID-19 cohort study will be used to assess treatment efficacy for binary, count and continuous data, using treatment arm as the main exposure variable of interest, and the stratification factors study site and presence of symptoms as co-variates in the crude analysis. Secondary analyses include covariate-adjusted analysis to determine whether the estimate of treatment-effect is affected with the inclusion of additional covariables, and per-protocol analysis, and sub-group analysis. Imputation for baseline missing covariates will be carried out before categorising. Assessment of the homogeneity of treatment effect by a subgroup variable will be conducted by a GLM with the treatment, subgroup variable, and their interaction term as predictors, and the P-value presented for the interaction term.

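### The nested trial's primary endpoint counts any negative Day-7 swab as clearance without requiring a positive baseline swab, its main model omits the baseline viral load already collected, and the Day-7 visit has two windows

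*Protocol*

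**What the plan says.** Section 4.3 (and the registration table in 2.2.3) gives the primary endpoint as "Incidence of SARS-CoV-2 clearance (defined as the proportion of participants with a negative nasal swab) on Day 7 after the start of treatment". The denominator is participants. Section 11.2.2.2 makes the primary population everyone randomised with valid consent, and 11.2.6.2 uses complete cases.

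Entry uses other tests. Section 6.2.2 accepts a positive antigen test, or a molecular positive from the past 72 hours, which sites with delays may extend to 120 hours. Section 9.1.1 adds: "If a participant tests COVID positive for any rapid antigen tests, GeneXpert, or PCR, the participant shall be enrolled". Footnote d of the schedule (2.2.4) accepts whatever diagnostic swab the local authorities use. The endpoint swab is a separate mid-nasal specimen, stored and tested later in batches (2.2.4 footnote j; 10.2.1), so its baseline result cannot decide entry. On that specimen the protocol notes: "Mid-nasal swabs were shown to have a sensitivity of 94% compared to nasopharyngeal swabs".

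Footnote n says that patients enrolled on Day 0 whose SARS-CoV-2 test turns out negative become screening failures without further follow-up.

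The main trial model uses "the stratification factors study site and presence of symptoms as co-variates in the crude analysis" (11.2.5.2). Covariate-adjusted analyses are secondary, with covariates unnamed.

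The schedule prints the Day-7 visit as (-2, +3) in its first header and (±1) in its second.

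**The concern.** Clearance means going from positive to negative. Someone negative on the research assay at enrolment has nothing to clear on that assay, yet a negative Day-7 swab makes them a success. Because these successes occur in both arms whatever the drug does, they pull the risk ratio towards 1. The protocol handles the parallel case differently: the note under the 4.3 table restricts seroconversion to participants who are antibody-negative on enrolment.

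Footnote n is only a partial safeguard. It concerns the diagnostic result in Day-0 enrolees. It does not reach the research swab, or patients who enter on an older molecular positive. It also sits awkwardly with 9.1.1, where any positive test enrols, and with an intention-to-treat population of everyone randomised.

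Two further points affect the same endpoint. The enrolment swab is assayed for viral load, a plausible predictor of Day-7 clearance, but the fixed primary model does not use it. And two current windows apply to the visit at which the endpoint is read.

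**Working it through.** **Inputs.** Section 11.1.3 plans on Day-7 clearance of 20% with artemether-lumefantrine and 42.2% with pyronaridine-artesunate, 5% dropout, 134 completers and a two-sided 5% level. Its claim is: "A study of 142 participants has 80% power to detect a 22.2% absolute increase in viral clearance by day-7". Allocation is equal (2.2.3), so there are 134/2 = 67 per arm. The baseline-negative share f is not in the documents; the range below is an assumption.

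**The plan's own figure.** Pooled z test: power = Φ{(d − 1.96·s0)/s1}, where d = 0.422 − 0.200 = 0.222.
- Mean rate = 0.311, so s0 = √(2 × 0.311 × 0.689/67) = 0.0800.
- s1 = √((0.200 × 0.800 + 0.422 × 0.578)/67) = 0.0776.
- (0.222 − 0.1568)/0.0776 = 0.84, and Φ(0.84) = 0.80.

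The stated 80% reproduces. It treats every completer as someone who can still clear virus.

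**Scenario A: baseline negatives have stopped shedding and stay negative.** Observed rate = f + (1 − f)p, with p = 20% and 42.2% among shedders. At f = 6%: 0.06 + 0.94 × 0.20 = 24.8% and 0.06 + 0.94 × 0.422 = 45.7%, so RR = 1.84. Excluding them restores 20% vs 42.2% with 67(1 − f) per arm.

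**Scenario B: baseline negatives are sampling misses, independent between visits.** These participants still shed. At Day 7 a fraction f of remaining shedders is missed, so the observed rate is p + f(1 − p), which is algebraically the same: 24.8% vs 45.7% at 6%. Excluding baseline negatives now leaves those diluted rates in place and only shrinks the sample to 67 × 0.94 ≈ 63 per arm.

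| f | Observed rates | RR | Power, all 67 per arm | Power after exclusion, A | Power after exclusion, B |
|---|---|---|---|---|---|
| 0 | 20.0% vs 42.2% | 2.11 | 80% | – | – |
| 3% | 22.4% vs 43.9% | 1.96 | 76% | 79% | 75% |
| 6% | 24.8% vs 45.7% | 1.84 | 72% | 77% | 69% |
| 10% | 28.0% vs 48.0% | 1.71 | 67% | 76% | 62% |

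**Baseline viral load.** In 2,000 simulated trials per setting (logistic model, 67 per arm, marginal rates held at 20% and 42.2%), adjustment took power from about 80% to 81%, 86% and 91% for an assumed log-odds slope of 0.5, 1.0 and 1.5 per SD. The slope is an assumption.

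**Window.** With a constant hazard (assumption), h = −ln(0.8)/7 and clearance by day d is 1 − exp(−hd). In the artemether-lumefantrine arm this gives 14.7% on day 5 and 27.3% on day 10, the limits of (-2, +3), and 17.4% on day 6 and 22.5% on day 8, the limits of (±1).

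**The case against.** The strongest objection concerns size and remedy. A reader might take the 94% sensitivity to mean that 6% of participants are negative at baseline and remain so, and that excluding them is sure to recover power. The documents do not support that. The figure compares sampling sites and suggests misses in people who still shed, which is scenario B, where exclusion costs a little power. The true share and its mix of A and B are unknown. This objection stands.

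The 20% planning rate may already include baseline negatives, since 11.1.3 applies it to the endpoint as defined. If both planning rates do, no power is lost relative to plan. If only the control rate does and the ratio of 2.11 holds among shedders, then at 6% the shedders' control rate is (0.20 − 0.06)/0.94 = 14.9%, the experimental arm is 0.06 + 0.94 × 0.149 × 2.11 = 35.5%, and power is 52%. The point cuts both ways and cannot be settled from the documents.

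Section 9.1.1 invites patients positive for both infections to enrol on Day 0, so the 72 to 120 hour delay may be uncommon in the trial, and footnote n removes some likely negatives. Both reduce f; neither sets it to zero.

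Naming covariates is commonly left to the SAP, and 11.2.5.2 allows for additional ones. A reader might infer that viral load is ignored altogether. It is not: it is a secondary endpoint and could enter the secondary adjusted analyses. What the protocol fixes is a primary model without it.

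The mid-nasal swab row sits under the (±1) header, and the rows under (-2, +3) cover screening and enrolment, so the conflict may be a table error. The day 5 to day 10 span is the extreme of the wider window and is not an expected effect on the comparison.

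Finally, the remedy needs a pre-dose swab. The schedule places it on Day 1 while treatment may begin on Day 0. Footnote a lets both fall on one day, but no passage states the order.

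**Conclusion.** The point holds as a should-fix. The endpoint as worded measures the proportion negative at Day 7, which equals clearance only if everyone is positive on the same assay at baseline, and nothing in the protocol ensures that. If baseline negatives have truly stopped shedding, counting them costs about 4, 8 or 13 points of power at 3%, 6% or 10%, and excluding them recovers most of it. If they are independent sampling misses, the dilution is the same and exclusion does not remove it. The case for an at-risk denominator therefore rests first on interpretability, and on power only under scenario A.

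A reader might infer a biased comparison or a higher false-positive rate. Neither follows: baseline status precedes treatment, randomisation balances it on average, and under no effect both arms are shifted equally. The trial is also described as exploratory. It nevertheless has a powered primary endpoint with an efficacy stopping boundary (11.2.5.3), so its definition should be settled.

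**What to change.** 1. Add baseline log10 viral load from the enrolment mid-nasal swab to the primary model beside site and symptoms, with negative swabs set at the detection limit. The value is already collected. The gain depends on how well it predicts clearance. If the log-binomial model fails to converge with a continuous covariate, 11.2.4.1 already provides a fallback.
2. Define clearance among randomised participants positive on the baseline research swab, taken before the first dose and read blind to arm, and report the all-randomised analysis alongside. State in the schedule that this swab precedes the first dose. The cost is a smaller set: about 63 instead of 67 per arm at 6% baseline-negative.
3. Reconcile footnote n with 9.1.1 and with the all-randomised population in 11.2.2.2, so that it is clear who is followed and who is analysed.
4. Reconcile (-2, +3) and (±1) into one Day-7 window counted from the start of treatment, as the endpoint wording already implies.

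These are mainly changes of wording and analysis; no new sample or assay is needed.
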